**7.2.4 Visit 6 – 6 weeks (42 ± 3 days)**

- Inquire about the occurrence of adverse events;
- Ask about the combined medication situation;
- Evaluation: MADRS, HAM-D17, HAMA, CGI-S, CGI-I and SDS;
- Evaluation: C-SSRS and ASEX;

- Vital signs: body temperature, respiratory rate, pulse and blood pressure (recumbent and standing);
- Weight measurement;
- Recover the remaining test drugs and packaging and record, release test drugs and record;
- Schedule the next visit and remind the subject to bring back the remaining test medications and packaging when they visit.

#### **7.2.5 Visit 7 – 8 weekends (56 ± 3 days)**

- Inquire about the occurrence of adverse events;
- Ask about the combined medication situation;
- Evaluation: MADRS, HAM-D17, HAMA, CGI-S, CGI-I and SDS;
- Evaluation: C-SSRS and ASEX;
- Physical examination: including general conditions, skin and mucous, lymph nodes, eyes, ear, nose, mouth, head and neck, thyroid, heart, lung, abdomen, spine, limbs, muscle, joint and nervous system examination;
- Vital signs: body temperature, respiratory rate, pulse and blood pressure (recumbent and standing);
- Weight measurement;
- 12-lead ECG;
- Pregnancy test (only women of childbearing age);
- Laboratory work: including blood routine, urine analysis, blood biochemistry, serology;
- Recover the remaining test drug and packaging and record.

#### **7.2.6 Early termination test**

Subjects may withdraw from the study at any time according to their wishes; the researcher or sponsor may require the subject to withdraw from the study at any time for safety reasons or because the subject is not be able to compliance with the follow up visit or procedure that required by the research program. If possible, the subject's last visit evaluation will be assessed according to the 8th weekend (visit 7).The subject's source documents and eCRF should be documented in detail for the reasons of termination.

## **8. Efficacy and safety evaluation**

### **8.1 Efficacy endpoint**

#### **The primary efficacy endpoint**

Changes from baseline in the Montgomery- Åsberg depression scales (MADRS) total scores at the end of treatment.

#### **The secondary efficacy endpoint**

- Changes from baseline in the 17 items Hamilton Depression Scales (HAM-D17) total scores at the end of treatment.
- Clinical Global Impression – global improvement (CGI-I) scores at the end of treatment.
- Changes from baseline in the Clinical Global Impression –severity illness (CGI-S) scores at the end of treatment.
- Changes from baseline in the the Hamilton Anxiety Scale (HAMA) total scores and factor scores at the end of treatment.
- Changes from baseline in the HAM-D17 factor scores at the end of treatment.
- Response rate in MADRS at the end of treatment (Response means that the reduction in MADRS score is 50% or more relative to the baseline value).
- Response rate in HAM-D17 at the end of treatment (Response means the reduction in the HAM-D17 scores is 50% or more relative to the baseline values).
- Remission rate in MADRS at the end of treatment (Remission refers to MADRS  $\leq 12$ ).
- Remission rate in HAM-D17 at the end of treatment (Remission refers to HAM-D17  $\leq 7$ ).
- Changes from baseline in the SHEEHAN Disability Scale (SDS) total scores at the end of treatment.

### **8.2 Safety evaluation**

- Adverse event
- Vital signs, physical examination, laboratory tests (blood routine, urine analysis, blood biochemistry, serology), 12-lead ECG
- Colombia - Suicide Severity Rating Scale (C-SSRS)
- Arizona Sexual Experience Scale (ASEX)

#### **8.2.1 Vital signs and weight**

Vital signs and weight should be checked during screening, baseline, follow up and early

termination of trials.

Weight (kg): can wear clothes and shoes, do not wear coats

Body temperature (°C)

Blood pressure (mmHg): supine position and standing position

Pulse (Times/minute): supine position and standing position

Respiratory (Times/minutes): Sitting in the state

Blood pressure and pulse measurement procedures: before measuring blood pressure, subjects should be required to not smoke or drink caffeinated beverages for at least 2 hours. Blood pressure should be measured with a mercury-based sphygmomanometer or an electronic sphygmomanometer that is suitable for the circumference of the subject's arm, and as much as possible pointed the same researcher to measure all subjects' blood pressure by the same side of arm throughout the study. For each visit, subjects should rest at least 2 minutes before measuring blood pressure (BP). 2 consecutive supine BP readings will be measured at a 2-minute interval. The supine pulse is measured in between the first BP measurement and the 2nd BP measurement, which ensures a pulse is measured within a 2-minute time period. After the 2nd supine blood pressure measurement, the subjects will rise and stand. After standing for 1 minutes, the 2 consecutive stand BP readings (2-minute interval) will be measured. The pulse in stand position will be measured at the time of after the first standing BP measurement and before the 2nd standing BP measurement, which ensures the pulse is measured within a 2-minute interval. The systolic and diastolic blood pressure levels were measured by Korotkoff I and V (vanishing). Each subject's vital sign measurements will as much as possible to obtain at the same time point at the each follow up visit and should be measured and determined by the same staff.

### **8.2.2 Physical examination**

Physical exam will be performed during the time of Screening; visit 7 and early termination of trials, including general appearance, skin, mucosa, lymph nodes, eyes, nose, mouth ears and head and neck, thyroid, heart, lungs, abdomen, spine and limbs, muscle and nerve system, and height will be performed in the screening.

### **8.2.3 12-lead ECG test**

A 12-lead electrocardiogram will be conducted during screening, visit 5, visit 7 and early termination of the trial, the participants should have a rest at least for 5 minutes before examination.

### **8.2.4 Laboratory work**

- 1) Safety labs will be drawn on screening, visit 5, visit 7 and early termination of the trial
  - Hematology: Complete blood count with differential (CBC) (hematocrit (HCT), hemoglobin, red blood cells (RBC), Red Cell Distribution Width (RDW), Mean

Corpuscular Volume (MCV), Mean Corpuscular Hemoglobin (MCH), Mean Corpuscular Hemoglobin Concentration (MCHC), platelets, white blood cells (WBC) with absolute differential counts of neutrophils, lymphocytes, monocytes, eosinophils, and basophils).

- Urine analysis: leukocyte esterase, pH value, nitrite, protein, ketone, bilirubin, blood, urine specific gravity, Glucose, urobilinogen,
  - Biochemistry: Total bilirubin, direct bilirubin, total protein, albumin, alanine transaminase, oxaloacetic Transaminase, alkaline phosphatase, gamma-transglutaminase, lactate dehydrogenase, creatine kinase, creatine kinase isoenzyme, urea nitrogen/urea, creatinine, uric acid, sodium, potassium, chlorine, total cholesterol, triglycerides, high-density lipoprotein cholesterol, low-density lipoprotein cholesterol, fasting blood sugar.
  - Serological: Prolactin (prolactin).
- 2) Laboratory screening indicators, only during the screening, including:
- Free T3 thyroid acid, free thyroxine, thyroid stimulating hormone
  - Hepatitis B Surface antigen, HCV antibody
- 3) Women of childbearing age will perform pregnancy tests on screening, visit 7 and early termination of trials.

All abnormal laboratory tests with clinically significant after the onset of the drug administration will be reviewed until the abnormal laboratory tests were returned to either normal or baseline or stable. If the abnormal laboratory result didn't not return to normal or return to baseline level or stability within a reasonable period of time, then the relevant causes should be identified and the sponsor should be notified.

### **8.2.5 Suicide Assessment-columbia-Suicide severity Rating Scale (C-SSRS)**

This scale is used for suicide risk assessment during screening, baselines, follow-up and early termination trials and should be screened using the "screening/baseline" scale and other follow-up using the "since last visit" scale.

### **8.2.6 Arizona Sexual Experience Scale (ASEX)**

The sexual function of the subjects was evaluated at baseline, follow up visits and early termination of the trial, and their sexual function changes were evaluated. This questionnaire is completed by the clinician or the person who is the subject of the test.

If the patient meet any one of the following, the patient may be considered to have sexual dysfunction: Asex total score of  $\geq 19$ , any asex scores  $\geq 5$  points, any 3 asex score  $\geq 4$  points. If the patient does not meet any of the above criteria, the sexual function may be considered normal.

### **8.2.7 Special precautions and Clinical intervention**

- 1) Deterioration of clinical symptoms and suicide

Major depressive disorder patients at any age, whether or not take antidepressants medication, are possibly to experience the worsening of the depression symptoms, increase the risk to have

suicidal ideation, suicidal attempt or abnormal behavioral changes, the symptoms can persist until a significant remission occurs. It is known that depression per se and certain mental disorders are associated with the risk of suicide, and these mental disorders themselves are the strongest predictors of suicide.

All subjects who treated with the drug (ansofaxine hydrochloride extended-release tablet or placebo) should be closely monitored any sign of deterioration of clinical symptoms, suicidal ideation and attempt and behavioral changes, especially in the early stages of drug therapy. When adults and children who have major depressive disorder, other psychiatric or non-psychiatric disorders treated with antidepressants medications, the following unexpected symptoms may occur: such as anxiety, agitation, panic attacks, insomnia, irritability, hostility, aggression, impulsivity, sedentary (psychomotor restlessness), hypomania and mania. Although the link between the onset of these symptoms and the deterioration of depression and/or suicidal impulses is not yet clear, these symptoms may be a precursor to suicide.

Participants who have continued to deteriorate symptoms of depression, commit suicide or suicidal ideation should consider discontinuing the test drug, especially for those who have serious symptoms, or who have had a sudden onset or new onset of symptoms.

In this trial, participants who have a risk of suicide should be excluded and, on each visit, the Colombian-suicide severity rating Scale (C-SSRS) should be assessed carefully to monitor the risk of suicide.

## 2) QTc interval prolongation

In vitro, ansofaxine hydrochloride inhibited hERG- encoded potassium channels which potentially cause QTc interval prolongation, however in the animal experiment of ansofaxine hydrochloride didn't showed QTc prolongation, In phase I tolerance clinical trials and phase II dose exploratory clinical trials didn't show QTc prolongation with clinically significant as well. In order to ensure the safety of the subjects, in this experiment, we should rule out the patients who have abnormal ECG with clinical significance (especially with the prolonged QTc), and ECG examination should be performed to monitor any abnormality of QT interval during the trial.

## 3) Blood pressure

Experimental study on cardiovascular safety of crab monkeys showed that the study drug can increase blood pressure in crab monkeys. But in phase I tolerance clinical trials showed that there was no blood pressure changes with clinically significant, however, in phase II dose exploratory clinical trial showed that a few subjects who have increased in blood pressure. In order to ensure the safety of the subjects, the effect of study drugs on blood pressure should be concerned, blood pressure should be closely monitored in this clinical trials in the position of supine and standing during each visit. Patients who have uncontrolled hypertension should be ruled out.

## **9. Safety reporting and procedures**

### **9.1 Adverse event**

#### **9.1.1 Definition of adverse events**

**Adverse event (AE)** is defined as any reaction, side effect, or untoward event that occurs during the course of the clinical trial whether or not the event is considered related to the treatment or clinically significant.

For this clinical trial, AEs will include any events reported by the patient, any new medical conditions, symptoms, any new abnormal findings on physical examination or laboratory evaluation. Additionally, any worsening of a pre-existing condition or abnormality will also be considered as an AE.

In this trial, adverse events occurred from the time that the subject signed the informed consent form to the last visit of the end of study were recorded.

Adverse events include, but are not limited to, the following situations:

- A non-existent adverse medical event at the time of signing the informed consent, which occurred in the course of the study;
- When signing the informed consent form, there is a combination of underlying diseases, aggravated in the course of the trial;
- Adverse events caused by special design of clinical study or intervention in the course of the study;
- Abnormal laboratory result with clinical significant based on the researcher's judgement.

Note: During the screening period with clinically significant laboratory abnormalities, if there is a reasonable and clear medical reasons to support the abnormalities occurred after the signing of the informed consent, then recorded as AE. If there is no medical reason to support it, it is recorded as a combined illness/ history of present illness.

#### **9.1.2 Criteria for severity of adverse events**

All AEs and clinically significant laboratory abnormalities will be graded as mild, moderate, and severe when filling out the eCRF adverse event table, the researcher will describe the extent of adverse events according to the criteri below.

Mild: asymptomatic or mild symptoms does not interfere with the subject's daily activities.

Moderate: to some extent interfere with the daily activities of the subject.

Severe: severely interferes with the subject's daily activities.

The severe adverse events and serious adverse events are different. The severity is a category that used to rate the grade of the event, adverse events and serious adverse events can be rated as severe. Headaches, for example, can be rated as severe, but cannot be list in the SAE unless it meet to the criteria of SAE.

### 9.1.3 criteria for judge the relationship between adverse events and test drugs

All adverse events should be evaluated for their relevance to the test drug, which is definite as definite, probable, possible, unlikely, unrelated to the incidence of adverse reactions.

$$\text{Adverse reaction rate} = \frac{\text{Number of cases with at least one}}{\text{Total number of cases used to assess}} \times 100\%$$

The criteria for determining the relationship between adverse events and test drugs are as follows:

**Certain:** evidence of the use of research drugs, the occurrence of adverse events and the use of research drugs have a reasonable time sequence, and adverse events are more reasonable to explain drug interpretation than other reasons. The drug withdrawal response was positive (adverse events disappeared after discontinuation of the drug), and repeated drug use (if feasible) was positive (reproduction).

**Probable related:** evidence of the use of research drugs, the occurrence of adverse events and the use of research drugs in a reasonable time sequence. Adverse events are more reasonable to explain drug interpretation than other reasons. The drug withdrawal response was positive.

**Possible related:** evidence of the use of the study drug, the occurrence of adverse events and the time dependence of the use of the study drug is reasonable. Adverse events can also be explained by other reasons. The drug withdrawal response was positive.

**Unlikely:** with evidence of the use of research drugs, the occurrence of adverse events is more reasonable to explain with other reasons. The withdrawal response was negative or unclear.

**Unrelated:** there is no correlation between the use of research drugs, or the timing of the use of research drugs and adverse events, or other causes that clearly lead to adverse events.

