Most of adverse events or adverse reaction were mild to moderate, clinical or diagnostic observations only; intervention not needed and self-recovered. Most common adverse events including nausea, decrease appetite, fatigue and dizziness. There were no statistically significant on the Arizona Sex Experience scale and the Columbia-Suicide severity Rating Scale (C-SSRS) between groups at each time point of follow up visit. The most common adverse events associated with drop-out were nausea, headache, and dizziness. Two patients in Ansofaxine hydrochloride extended-release 40mg group were reported to have had severe adverse events: one patient had hypomania and one patient had worsening of the symptoms of depression, both of them were considered relevant to the study drug, follow up to the stable condition. No death occurred in this study.

Phase II clinical trial result showed: The efficacy, safety and tolerability of Ansofaxine hydrochloride extended-release tablets in the range of 40-160 mg superior to the placebo group.

This clinical trial was conducted in accordance with the clinical trial approval issued by the State Food and Drug Administration (CFDA) on June 16, 2015 (Approval No.: 2015L01158/2015L01159/2015L01160/2015L01161).

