#### 6.5 Dosage adjustment

Change the dosage is not allowed in the clinical trial.

The subjects may be suspended if subjects experience adverse events and was agreed to by the investigator, the subjects will get other treatment based on investigator's judgement.

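### Section 9.1.3 requires a positive withdrawal response for every related category, so an event that resolves on continued drug cannot be rated related

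*Protocol*

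**What the plan says.** Section 9.1.3 grades causality on five levels and applies them to every event: "All adverse events should be evaluated for their relevance to the test drug". Three levels express a relationship, and each includes a positive withdrawal response.

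- Certain: "The drug withdrawal response was positive (adverse events disappeared after discontinuation of the drug), and repeated drug use (if feasible) was positive (reproduction". This is also where a positive response is defined.
- Probable: "adverse events are more reasonable to explain drug interpretation than other reasons. The drug withdrawal response was positive".
- Possible: "Adverse events can also be explained by other reasons. The drug withdrawal response was positive".

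Unlikely has two conditions. On cause, "the occurrence of adverse events is more reasonable to explain with other reasons". On withdrawal, "The withdrawal response was negative or unclear".

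The feasibility qualifier in Certain belongs to rechallenge. The withdrawal response has no such qualifier and no not-applicable option.

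Three other places bear on how often a withdrawal response will exist:

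- Section 6.5: "Change the dosage is not allowed in the clinical trial". The same section lets a subject be suspended after an adverse event if the investigator agrees.
- Section 1, Phase II clinical trial: "Most of adverse events or adverse reaction were mild to moderate, clinical or diagnostic observations only; intervention not needed and self-recovered".
- Section 7.2.5: the last scheduled visit is week 8, at the end of treatment. Section 9.1.5 has events followed until they resolve, stabilise or are otherwise closed.

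Section 11.2.2.5 summarises drug-related and unrelated events and compares them by Fisher's exact test. It also tabulates related treatment-emergent events by system organ class and preferred term.

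**The concern.** A withdrawal response exists only if drug was stopped while the event was present. An event that comes and goes during continued dosing has none. Early nausea that settles on treatment is the natural example: nausea is among the most common events reported from phase II. Such an event may be clinically attributable to drug and still fail the written test for Certain, Probable and Possible.

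Safety is the secondary objective (Section 2), and the related-event tables and the adverse reaction rate are built on this classification. The call is made at site from Section 9.1.3, so no later analysis rule can recover a judgement that was never recorded.

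**Working it through.** The protocol gives no figure on this point to reproduce. The check is a comparison of the five definitions, followed by an illustration.

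**Step 1. The definitions side by side (Section 9.1.3).**

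| Category | Drug versus other causes | Withdrawal response |
|---|---|---|
| Certain | drug the better explanation | positive, and rechallenge positive if feasible |
| Probable | drug the better explanation | positive |
| Possible | other causes could also explain it | positive |
| Unlikely | another cause the better explanation | negative or unclear |
| Unrelated | no link in use or timing, or another clear cause | none stated |

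**Step 2. Place an event with plausible timing that resolves while the patient stays on drug.** There was no discontinuation, so there is no positive response as Section 9.1.3 defines it.

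- Certain, Probable and Possible all fail on the withdrawal condition.
- If another cause is the better explanation, the event can go to Unlikely, reading an absent response as unclear.
- If drug is the likelier cause, Unlikely fails on its first condition and Unrelated fails on timing. No category fits, although every event must be graded.

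**Step 3. Will such events occur?** Dose changes are ruled out, suspension is optional, and phase II events mostly resolved without intervention. Some events will therefore have no withdrawal response. The protocol does not give the share.

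**Step 4. Illustration only.** Let q be the share of patients with an adverse reaction who have at least one reaction with a positive withdrawal response. q is an assumption. The phase II adverse reaction rates (Section 1) are placebo 38.78%, 80 mg 65.38% and 160 mg 62.75%. Rate under the literal rule = q × phase II rate.

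| q | Placebo | 80 mg | 160 mg | 80 mg − placebo | 160 mg − placebo |
|---|---|---|---|---|---|
| 1 | 38.8% | 65.4% | 62.7% | 26.6 points | 24.0 points |
| 0.75 | 29.1% | 49.0% | 47.1% | 20.0 | 18.0 |
| 0.50 | 19.4% | 32.7% | 31.4% | 13.3 | 12.0 |
| 0.25 | 9.7% | 16.3% | 15.7% | 6.7 | 6.0 |
| 0.10 | 3.9% | 6.5% | 6.3% | 2.7 | 2.4 |

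For example, at q = 0.50 and 80 mg: 0.50 × 65.38% = 32.7%. With the same q in every arm, the differences shrink in proportion and the ratios between arms do not change. The causality criteria used in phase II are not given, so the table shows direction and sensitivity and is not an estimate.

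**Step 5. What does not depend on the scale.** Section 11.2.2.5 also summarises all treatment-emergent events, serious events and events leading to withdrawal. None of these uses the causality grade.

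**The case against.** The strongest case on the other side has four parts.

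- *Misclassification need not run downward.* Because Unlikely needs another cause to be more reasonable, a probable drug effect is not forced into it. Investigators faced with no fitting category may simply use judgement. This stands. It turns a certain understatement into either understatement or inconsistency between sites, and neither serves the planned tables.
- *Withdrawal information is not that rare.* Section 6.5 allows suspension, every completer stops drug at week 8, Section 9.1.5 continues follow-up, and Section 1 names nausea, headache and dizziness as the most common events associated with drop-out. This also stands, and it is why no size can be fixed. It does not help an event that resolves before drug is stopped.
- *Phase II produced high reaction rates anyway.* Dividing the reaction rate by the event rate gives 65.38/75 = 87% at 80 mg and 62.75/68.63 = 91% at 160 mg, although most events resolved without intervention. Since the phase II criteria are not stated, this neither supports nor refutes the point.
- *The consequences are limited.* Section 11.2.2.6 makes safety P values nominal, and the summaries that do not use causality carry much of the safety objective. This stands.

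Three stronger readings are tempting and are not supported:

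- A reader might assume that 5–15% of patients with an event stop drug and infer a ceiling on the reaction rate of roughly 3–11%. That share is nowhere in the protocol, and the calculation ignores suspension and follow-up after week 8.
- A reader might infer that the loss falls mostly on the active arms. The same rule is applied blind in all arms, and placebo had 38.78% reactions in phase II.
- A reader might infer that expedited reporting is affected. In the text at hand SUSAR appears only in the abbreviation list, and Section 9.2.2 requires every serious event to be reported within 24 hours whether or not it is related.

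**Conclusion.** The point holds as a defect in a stated rule. Read literally, Section 9.1.3 prevents an event that resolves on continued drug from being rated related, and leaves a drug-attributable event of this kind without any category. The related-event summaries and comparison in Section 11.2.2.5 and the adverse reaction rate will be too low if sites follow the text, and inconsistent if they do not. The size cannot be derived from the protocol.

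Two assumptions apply. Related is taken to mean Certain, Probable or Possible, because the numerator of the adverse reaction rate is cut off in the copy at hand. The text is also taken to be what investigators apply. The condition is repeated in three categories and contrasted with its opposite in the fourth, so a slip of translation in a single sentence is an unlikely explanation.

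The efficacy analysis and the safety summaries that do not use causality are untouched. This should be corrected, but it does not undermine the trial.

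**What to change.** Reword Section 9.1.3 and the matching eCRF guidance as follows:

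- A withdrawal response that was not assessed, not applicable or unclear does not by itself exclude Possible or Probable.
- A positive withdrawal response is required only where drug was actually stopped.

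Nothing in dosing, suspension or withdrawal needs to change. The cost is a wording amendment and a short briefing of investigators. If any events have already been graded under the present text, their grades should be reviewed while still blinded. The reported adverse reaction rate may become less favourable.
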